#### Methods of data analysis

The audio taped interviews will be transcribed verbatim and imported as text documents into the qualitative analysis program, NVivo 2.0, that will be used to code and analyze the data. Analysis will be performed by using qualitative content analysis with a directed approach. Directed content analysis is aimed at validating or conceptually extending a theoretical framework. Existing theory serves as a basis for an initial coding scheme. Each code is accompanied by a specific definition which is derived from the theory [19,20]. Our coding scheme will reflect the concepts of the HBM [9,12] and the TPB [10]. The initial coding scheme will be developed by two researchers (JG and MI) and will cover the topics of the interview route (e.g. self-testing in general, reasons for testing, performing the self-test, information, and follow-up behaviour) and prompts (e.g. barriers, benefits, self-efficacy). Furthermore, free codes will be formulated to label additional topics that emerge during data-analysis.

Two researchers (JG and MI) will independently code all interviews. Meetings will be held in order to check the coding on exhaustiveness and appropriateness. Furthermore, it will be verified whether all theoretical concepts are identified and correctly categorized. Disagreements will be solved by comparing the text fragments and the conceptual definitions of the codes until consensus is reached. If consensus is not reached, a third independent rater will be appointed in order to achieve consensus (GR). Finally, all free codes will be integrated in the original coding scheme that is conceptually similar to the HBM [9,12] and TPB [10]. If these free codes appear to be a separate concept, the theoretical framework will be extended.

After coding is completed, the results for the different self-tests will be compared and assessed on their similarities. If certain self-tests are conceptually similar to one another, clusters will be made based on diseases and risk factors, (e.g. a cluster for CVD and related risk factors consisting of diabetes and cholesterol tests or a cluster for STDs consisting of Chlamydia and HIV). Analyses will result in a description of self-test behaviour, information needs and use of consumers, and their follow-up behaviour based on the test-result.

### Study 3: Assessment of the quality of consumer information of self-tests

#### Aim

The purpose of this study is to assess the quality of the instruction leaflets that are included in diagnostic self-test kits for home-use that are available on the Internet (research question 6).

#### Selection criteria

We will only include diagnostic self-tests for home use on body materials with the aim to diagnose a certain disease or risk factor. The home-tests under consideration will be the top-5 most frequently used self-tests in the Netherlands [1].

#### Methods of data collection

Dutch and English consumer information concerning the selected set of self-tests will be collected. First, we will perform an Internet search using Google which will only be aimed at websites which are available in Dutch or in English. If more than one producer has marketed one specific test, all available types will be included. The following key words will be used: selftesting, selftest, self test, home test, laboratory test, point-of-care test, direct-access test, lab test, home collect test. Additionally, we will search the Internet for specific tests and/or producers. The first 7 pages that come up at each key word will be consulted. If relevant links are identified in one of these pages, these sites will also be consulted. An overview will be made of the different test kits. The available consumer information will be downloaded from the Internet. Second, if the consumer information is not available on the Internet, producers or suppliers of self-tests will be contacted in order to collect this information.

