## Background

A range of self-tests has become available to consumers in the Netherlands and elsewhere [1]. Self-tests are currently available for more than 25 conditions, ranging from infectious diseases to cardiovascular risk factors. Self-tests are not rarely used; 16% of a sample of Dutch Internet users indicated they had ever used at least one self-test in 2006, whereas 17% of those who had never used a self-test indicated they would probably or definitely use one in the future. The five most frequently used self-tests were tests for diabetes, cholesterol, allergies, urinary tract infection, and HIV [1].

We defined self-tests as in-vitro tests on body materials such as blood, urine, faeces, or saliva that are initiated by consumers to diagnose a particular disorder or risk factor. In other words, by using a self-test, consumers completely avoid the traditional health care systems. Pregnancy tests, home blood-pressure meters, and monitoring tests, e.g. serum glucose for patients with diabetes mellitus to follow-up on their disease and therapy, are examples of tests that are excluded by this definition. Self-tests can be subdivided into four distinct types that are directly accessible to consumers without the need for a preceding consultation with a doctor [1]. The first type of self-test concern self-tests for home use or the over-the-counter tests, in which the consumer is responsible for the execution and interpretation of the test as well as their follow-up behaviour. The second type of self-test comprises self-tests that are offered by an organization which carries out the test in public areas such as local supermarkets and the results are presented immediately. These tests are the so-called street-corner tests like the national cholesterol test offered by the Dutch Heart Association [2]. The third and fourth self-test categories include tests in which a consumer attends a laboratory facility to have body material taken (direct-access laboratory test) or sends body material to a laboratory where the test is executed (home-collect test), after which the result is sent to them by mail or via the Internet.

Four separate phases can be distinguished within the self-test procedure, namely (1) the decision process preceding the performance of a self-test, (2) the actual execution of the self-test (only applicable to over-the-counter tests), (3) the interpretation of the test-result, and (4) the consumers' follow-up behaviour based on the test-result.

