#### Methods of data analysis

A checklist will be developed based on the validated English version of the International Patient Decision Aids Standard (IPDAS)[21,22], the DISCERN criteria [23,24], and the Dutch regulations for content of IVD patient information [25,26]. Additionally, items derived from the Internet survey and qualitative research will be included (e.g. which information is important according to consumers). The research team will be asked to assess the resulting initial and provisional checklist and to provide suggestions for improvement. Based on these comments, the checklist will be adapted and will be reviewed by the research team once again. If written comments are unclear, the specific member of the research team will be consulted for additional oral comments.

The checklist will be tested for its usability by applying the list on consumer information that was collected in the Internet search. Two researchers will each code three different leaflets of users' instructions. Each criterion will be coded on a 5-point Likert-scale which ranges from 1 = *definite no - the quality criterion has not been fulfilled at all*, to 5 = *definite yes - the quality criterion has been completely fulfilled*. The researchers have the opportunity to indicate if they perceived any problems when applying the checklist. Potential problems or suggestion for better use will be incorporated in the final version of the checklist.

Finally, the consumer information will be coded by means of the checklist. Furthermore, cut-off points will be determined to establish the overall quality level of the information. Two coders will independently code each leaflet of consumer information that was identified. Consensus meetings will be held in order to reach valid judgment of the quality of the consumer information.

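### Study 3 seeks Dutch and English leaflets but lists only English key words, so Dutch leaflets may be missed

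*Protocol article*

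**What the plan says.** All references are to the Protocol article.

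- **Languages sought** (Study 3, Methods of data collection): "Dutch and English consumer information concerning the selected set of self-tests will be collected". The Google search is to "only be aimed at websites which are available in Dutch or in English".
- **Key words** (same section): "The following key words will be used: selftesting, selftest, self test, home test, laboratory test, point-of-care test, direct-access test, lab test, home collect test". The first seven pages are read for each key word.
- **Other routes** (same section): a further search on specific tests or producers, the following of relevant links, and contact with producers or suppliers when a leaflet is not online. Where several producers sell the same test, all versions are to be included.
- **Eligibility** (Selection criteria, under Study 3): "We will only include diagnostic self-tests for home use on body materials with the aim to diagnose a certain disease or risk factor". Five tests qualify, namely those used most in the Netherlands.
- **Test types** (Background): home-use tests are the first of four types: "The first type of self-test concern self-tests for home use or the over-the-counter tests". Direct-access laboratory tests and home-collect tests are the third and fourth.
- **Scoring** (Study 3, Methods of data analysis): each criterion is rated from 1 to 5, and cut-offs will set the overall quality level. The checklist draws on IPDAS, DISCERN and "the Dutch regulations for content of IVD patient information", with items added from the survey and interviews.

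**The concern.** The search string does not match the stated target. Half of the language scope is Dutch, yet no printed term is Dutch. A Dutch site that describes its product only as a *zelftest* or *thuistest* need not appear under any of the nine terms. Restricting results to Dutch or English sites does not cure this, because a filter removes hits and does not supply query words.

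Two things are at stake. The first is completeness: the plan wants every producer's version of each test, and the findings are to be the basis for new consumer information. The second is interpretation. Dutch regulations feed the checklist, but nothing in the article separates leaflets for kits sold to Dutch consumers from English leaflets written for other markets. A low score on a Dutch-regulation item could then mean that the kit was made under other rules, rather than that its information is poor.

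**Working it through.** There is no sample size or error rate to reproduce here. The check is a count of the printed terms, the page arithmetic, and a look at what each other route can find.

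**1. The nine terms, classified with the types defined in Background**

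| Term | Dutch? | Names a type other than home use? |
|---|---|---|
| selftesting | no | no |
| selftest | no | no |
| self test | no | no |
| home test | no | no |
| point-of-care test | no | arguable |
| laboratory test | no | yes |
| lab test | no | yes |
| direct-access test | no | yes |
| home collect test | no | yes |

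Dutch terms: 0 of 9. Terms for types outside home use: 4 of 9, or 5 of 9 if point-of-care is counted.

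**2. Pages read in the key-word search**

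- Total: 9 terms × 7 pages = 63.
- From terms for ineligible types: 4 × 7 = 28 (or 5 × 7 = 35).
- From the remaining terms: 5 × 7 = 35 (or 4 × 7 = 28).

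The limit is seven pages for each key word. If the ineligible-type terms were deleted, the other terms would still yield the same 35 (or 28) pages. The ineligible terms therefore cost reading time and take no place from eligible kits. The 63 pages also leave out the test and producer search and any followed links, so they are not the whole of what will be read.

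**3. What the other routes can recover**

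- *Search by test or producer.* This is the one route that could find Dutch kits independently of the key words. The article gives neither its terms nor its language. Of the five tests named in Background, the words diabetes, cholesterol and HIV are spelled alike in Dutch and English, so such a search may well reach Dutch pages. Nothing in the text guarantees it.
- *Following links.* This starts from pages already found, so it depends largely on the terms that found them.
- *Contacting producers or suppliers.* As worded, this obtains a leaflet that is not online. It presupposes that the kit or supplier is already known.

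**4. Size of the loss**

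The share of Dutch leaflets missed would be the number of eligible Dutch leaflets not found divided by the number that exist. The article gives neither figure, nor any count of leaflets by language, so no value or range can be calculated.

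**The case against.** The strongest reply is that the article is in English and the list may be a translation of Dutch search strings, with the exact strings left to a fuller document. That is possible, but the article does not say so. It prints the terms as those that will be used, with variants such as *selftest* and *self test* entered separately. That reads like literal search strings, though it does not settle the matter. If the list is a translation, stating this and giving the actual terms still makes the search reproducible.

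It can also be said that the key words are one route among several. This stands, and it is why under-retrieval is a risk and not a demonstrated result.

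A reader might infer three stronger things, none of which the article supports:

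- *That the terms for laboratory, direct-access and home-collect tests crowd out eligible kits.* They cannot, because the page limit is per key word.
- *That research question 6 concerns only information for Dutch consumers.* As stated it has no such limit. Dutch usage selects the five tests, and English leaflets are included by design.
- *That the collected set will be mostly English and the quality judgement therefore biased.* No figure in the article shows this. Dutch regulations are one of three named checklist sources, and the checklist is still to be developed, so the weight of the Dutch-specific items is unknown.

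Scoring other-market leaflets on Dutch rules is also not caused by the key words. It follows from including English leaflets, and would remain after Dutch terms were added. It needs its own remedy.

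**Conclusion.** The concern holds in a limited form. As printed, 0 of 9 key words are Dutch although Dutch information is sought, so the key-word search risks missing Dutch leaflets unless the unspecified test and producer search finds them. This assumes that the list is run as written and that some Dutch sites do not use the English terms. The size of the loss cannot be computed.

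The four (or five) terms for ineligible test types are a matter of efficiency only: 28 (or 35) of 63 key-word pages spent on hits to be screened out.

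Separately, the described analysis would rate leaflets from other markets on items drawn from Dutch regulations without distinguishing them. How far that moves the overall quality level depends on a checklist not yet developed. Both points are cheap to settle before the search and coding begin, and harder to repair cleanly afterwards.

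**What to change.** 1. **Add Dutch key words**, for example *zelftest* and *thuistest*. They may replace the terms for ineligible test types. If the printed list is a translation, say so and give the terms actually used.
2. **Run the test and producer search in both languages**, and state its terms.
3. **Record for each leaflet whether the kit is sold to Dutch consumers.** Report checklist scores separately for those kits and for other English-language leaflets, and apply items based on Dutch regulations only to the former. The overall cut-offs must then allow for the different number of applicable items in the two groups.

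**Cost.** Each added key word brings 7 pages. Two added terms give 63 + 14 = 77 pages, and four give 63 + 28 = 91. Four Dutch terms in place of the four ineligible-type terms keep the total at 63. Running the test and producer search in Dutch as well adds pages that cannot be counted, because its extent is not stated. Crossing the Dutch key words with test names is not proposed, because it would be much heavier: four terms with five names is 4 × 5 × 7 = 140 pages, and with ten names (each test in both languages) 4 × 10 × 7 = 280. A few more leaflets may need double coding, and the market of each kit must be established when it is collected.

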#### Methods of data analysis

A checklist will be developed based on the validated English version of the International Patient Decision Aids Standard (IPDAS)[21,22], the DISCERN criteria [23,24], and the Dutch regulations for content of IVD patient information [25,26]. Additionally, items derived from the Internet survey and qualitative research will be included (e.g. which information is important according to consumers). The research team will be asked to assess the resulting initial and provisional checklist and to provide suggestions for improvement. Based on these comments, the checklist will be adapted and will be reviewed by the research team once again. If written comments are unclear, the specific member of the research team will be consulted for additional oral comments.

The checklist will be tested for its usability by applying the list on consumer information that was collected in the Internet search. Two researchers will each code three different leaflets of users' instructions. Each criterion will be coded on a 5-point Likert-scale which ranges from 1 = *definite no - the quality criterion has not been fulfilled at all*, to 5 = *definite yes - the quality criterion has been completely fulfilled*. The researchers have the opportunity to indicate if they perceived any problems when applying the checklist. Potential problems or suggestion for better use will be incorporated in the final version of the checklist.

Finally, the consumer information will be coded by means of the checklist. Furthermore, cut-off points will be determined to establish the overall quality level of the information. Two coders will independently code each leaflet of consumer information that was identified. Consensus meetings will be held in order to reach valid judgment of the quality of the consumer information.

## Discussion

Self-testing is a relatively new area and is still in a state of flux. Since the start of our 2006 study, we have observed a shift in the self-testing area. In 2006, most self-tests were at the consumer's own expense. In the last few years we observed that associations like the Dutch Kidney Association and the Municipal Health Services actively offer free self-tests to the Dutch public to detect kidney disease or Chlamydia infection. Media campaigns alert the Dutch public on the option to order a self-test for kidney disease or the target group receives an invitation by mail to order a self-test for Chlamydia. The tests are sent at no charge to the home of all individuals who request for it on a website [27,28]. We consider this a grey area in between pure self-diagnosis on the consumer's own initiative and testing initiated by a professional. Furthermore, some of the larger Dutch Health Insurance Companies partly compensate for the costs of a self-test. As a result of these developments in combination with the increase in Internet use and the current development of patient autonomy in health care, it is expected that self-tests are likely to become even more easily available and more widely used.

The studies described in this protocol are characterized by some innovative aspects. First, information about self-testing is scarce. Most studies on self-testing have focused on socio-demographic characteristics [1,2,5,8,29-32] of self-testers and technical aspects of self-tests [33-39]. To the best of our knowledge, studies concerning the considerations of individuals who intend to perform a self-test are lacking. In our opinion, this group is still undecided about performing or not performing a self-test and therefore has the highest information needs concerning self-testing. It is important to guide these individuals in making an informed choice about performing or not performing a self-test. Second, by combining quantitative and qualitative studies into a mixed-methods design, we aim to gain both general and more in-depth insight into considerations of self-testers and individuals who intend to perform a self-test.

By using an Internet research institute we are able to reach a large group of individuals which is necessary to gain insight into the general public's considerations about self-testing. On the one hand, it can be argued that using an Internet panel may result in a selection bias because these are individuals who are highly motivated to participate in surveys and who might be more concerned with their health. On the other hand, studies on Internet surveys versus paper-and-pencil surveys indicate that Internet surveys may yield similar results as traditional paper-and pencil surveys [40-42]. The Internet panel is not completely representative of the general Dutch population as panellists are slightly younger, more often female and more highly educated [1]. However, the Internet research institute claims that their panel is representative of the Dutch Internet population and since most self-tests are bought via the Internet, we consider the use of this panel as an acceptable option.

From a methodological perspective, a large scale Delphi study would have been optimal to develop the checklist assessing the quality of the consumer information about self-testing. However, due to financial and logistic restrictions, we use a small scale Delphi study consisting of experts of our research team. We believe that the checklist will have satisfying face-validity, is evidence-based, and is well-founded in theory since the checklist will be based on the results of our 2006 study, the results of studies one and two described in this protocol, and on the IPDAS criteria for decision aids [21,22], the Discern criteria for judging the quality of written consumer information on treatment choices [23,24], and the Dutch regulations for content of IVD patient information [25,26].

The study will allow us to get more insight into the considerations of self-testers and individuals who intend to perform a self-test and on the quality of the currently available consumer information. As far as we are aware, this will be the first study which focuses on these different aspects of self-testing simultaneously. The findings from the studies described above will provide the basis for new to develop consumer information on self-testing which will be tested on its effectiveness using an RCT. The development process and the outline of the RCT will be described in a second study protocol.

## Abbreviations

CVD: Cardiovascular diseases; HBM: Health Belief Model; IPDAS: International Patient Decision Aids Standard; ISO: International Organization for Standardization; IVD: In-Vitro Diagnostics; STD: Sexually transmitted diseases; TPB: Theory of Planned Behaviour; RCT: Randomized Controlled Trial

